### Unblinding procedures

In the event of medical emergency that requires identification of an individual patient’s treatment, blinded investigators will be allowed to contact the unblinded investigator or peruse the anesthesia protocols. The reason must be documented in the patient’s medical record and eCRF and must explain why revealing the treatment assignment was essential to guide subsequent intervention and therapy.

### Data collection methods

The coordinating principal investigator will ensure local training to enhance the data collection quality and reduce bias. The investigator will ensure that all assisting study personnel will be adequately qualified and informed about the study protocol, any amendments, study medication and study related responsibilities and functions. The investigator will maintain a study staff authorization log.

Each center will provide a stopwatch with minutes and seconds to measure awaking times. The modified Aldrete Score and PQRS form are enclosed in the Additional file 2 and 3 of the study protocol. After an initial pilot study of 133 patients, the PQRS tool was revised to its current form, and a validation study of 701 participants was conducted [9]. The VAS and VRS scales are valid, reliable and appropriate for use in clinical practice [10]. Once a patient is enrolled or randomized, the study site will make every reasonable effort to follow the patient for the entire study period until completion of phase G.

### Premature treatment termination

The study will be terminated prematurely (dropout) for an individual subject if the following occurs: serious intraoperative anesthesia complication, with required postoperative transfer to intensive care unit for anesthesiological reasons. The time point and specific reason for premature treatment termination of each subject have to be documented. The investigator shall determine a fundamental reason for premature treatment termination of each subject. All relevant safety data until subject’s treatment termination will be collected and reported. The study will be terminated in the event the risk-benefit-ratio alters in such a way, that premature treatment termination is indicated to protect a subject’s health.

### Premature study termination

Participants may withdraw from the study for any reason at any time. As the follow-up period in this study is only one day, we do not expect many withdrawals. These withdrawals could only imply missing data for the PQRS testing at T40 and on 1^st^ POD.

### Data management

Standardization procedures will be implemented to ensure accurate, consistent, complete and reliable data, including methods to ensure standardization among sites (for example, training, newsletters, investigator meetings, monitoring, centralized evaluations, and validation methods). The monitors will be trained during a kick-off meeting. Preparatory training to prepare the investigators and to standardize performance will be held during an investigators’ meeting before study start. This study will be monitored regularly by a qualified monitor from the sponsor Clinical Trial Center Aachen (CTC-A) according to the good clinical practice (GCP) guidelines and the respective SOPs (see Section Monitoring).

All data collected from a subject during the course of this clinical study have to be entered and/or filed in the respective subject file (CRF, case report forms). These data will be considered as source data. The subject file must contain a detailed statement on the informed consent procedure. The subject’s participation in this study must be appropriately documented in the subject file with study number, subject number, date of subject information and informed consent, date of each visit, and date of a potential telephone contact. If a study site is using an electronic system for documenting source data, a member of the site staff must print out the source data after each visit. The paper printouts must be overlapping, if possible (for example, must contain at least the last row of data from the subject’s previous visit). Otherwise, the thoroughness of source data must be ensured by other suitable means. The printout must be signed and dated by a member of the site staff who can confirm the accuracy and completeness of data in the paper printout. Additionally, the monitor shall sign and date the verified paper printout. The paper printout shall be stored in the investigator site file (ISF). If the source data information is entered retrospectively, it must be done directly on the paper printout and must be initialed and dated. The same applies to any corrections of initial data. Paper printouts are not required if the site is using a validated computer system, including audit trail, with separate access for the monitor (for example, monitor has solely access to data of the study subjects). If corrections are necessary, the subject shall be instructed to draw a single line through the error, leaving the incorrect entry legible. The subject should date the correction, but not initial it. The investigator shall not falsify the documents. The sponsor’s data management function will be responsible for data processing in accordance with the sponsor’s data management procedures. Database lock will occur only after quality assurance procedures have been completed.

All source data related to study data should be kept in locked cabinets. Access to the study data will be restricted. Investigators will enter the information required by protocol into an electronic data collection system via internet (eCRF). The study data manager will develop the eCRF. Detailed information on the eCRF completion will be provided during the site initiation visits. An eCRF completion manual will be provided to each site. An e-learning tool will train all persons who enter data into the eCRF. After the successful completion of the training, all participants will receive a training certificate. The access to the e-learning tool and to the eCRF will be password-controlled. Plausibility checks (including valid values, range checks, and consistency checks) will be performed according to a data validation plan to ensure correctness and completeness of these data. Inconsistencies will be queried via the electronic data collection system; answers to queries or changes of the data will directly be documented in the system. The database will be closed after all data are entered and all queries are solved. By signing the CRF (eCRF/eSignature), the investigator will confirm that all investigations have been completed and conducted in compliance with the clinical study protocol, and that reliable and complete data have been entered into the eCRF. The investigator will keep the subject files and original data as long as possible and according to the local procedure, but at least for 10 years, as specified in the International Conference on Harmonisation, (ICH)-GCP Guideline. The investigator/institution should take measures to prevent accidental or premature destruction of these documents.

### Statistical methods

All efficacy, safety and economical results will be presented on the Intention to Treat (ITT) data set, which will be composed of all randomized patients. In case it appears necessary, we will define a secondary Per Protocol (PP) data set prior to the database lock. The PP would be a subset of the ITT data set, composed of all randomized patients who have no major protocol deviations throughout their entire study period. This PP data set would be used for the secondary supportive analysis of the primary efficacy criterion and serve as a check of its robustness.

Parametric data will be analyzed with ANOVA and nonparametric data with the two-tailed Fisher’s exact test if incidence <5 or the Chi-square test with incidence >5. The inference for the noninferiority will be based on the upper confidence bound. A fully specified Statistical Analysis Plan will be made public before unmasking results. Additional analyses are not planned.

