Maintenance: All patients will receive a postoperative nausea and vomiting (PONV) prophylaxis with 8 mg dexamethasone and 4 mg ondansetron, if the Apfel-Score is ≥2. Analgesia will be maintained with remifentanil injection via infusion pump at a rate of 0.15 μg kg^−1^ min^−1^. Dosage will be adapted according to clinical needs based on the patient’s hemodynamic (difference of NIBP and HR greater than 20 % from baseline), autonomic (sweating, salivation, or flushing) and somatic (movement or swallowing) signs. Twenty minutes before the estimated end of surgery, all patients will receive 0.05 to 0.1 mg kg^−1^ piritramide and 15 mg kg^−1^ metamizole i.v. The inspired oxygen concentration will be adjusted to 35 to 50 %, or above this range if medically indicated. The end-expiratory CO_2_ level during the maintenance of anesthesia should be kept between 36 and 45 mmHg. The use of muscle relaxants is undesired, except for emergency situations. Spontaneous breathing or controlled ventilation with LMA will be applied during maintenance of anesthesia, according to the standard operating procedure of each participating center. Inspired desflurane concentrations of >8 vol. % and sevoflurane >2.2 vol. % have to be avoided. The systolic blood pressure should be kept at ≥90 mmHg (or ≥65 mmHg for mean arterial blood pressure), and a relative variation > 20 % from baseline values has to be avoided and requires appropriate treatment. If indicated additional bolus injection of propofol is permissible in patients.

End of anesthesia: At five minutes before planned termination of surgery, remifentanil will be discontinued. The LMA will be removed when the upper airway reflexes are fully recovered and the respiratory function is adequate (regular spontaneous breathing with a frequency of at least eight breaths per minute and SaO_2_ >95 %) and when the patient opens his/her eyes on request or is able to follow any other requests. In addition, the patient has to be hemodynamically stable before removal of LMA. The patients will be admitted to the Post Anesthesia Care Unit (PACU) following surgery. They will receive 0.05 mg kg^−1^ piritramide if the visual analog scale (VAS) for pain is more than 30.

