### Outcomes

#### Primary outcome measures

The primary objective of this trial is to investigate, whether the emergence time until the stating of the date of birth after desflurane anesthesia is superior to the time after sevoflurane or propofol anesthesia. The selection of stating the date of birth as the primary clinical outcome variable is associated with the result of our latest meta-analysis [4]. This meta-analysis supposes faster emergence times in the desflurane-treated patients, but the included studies had only small sample sizes ≤65 patients per group. Furthermore, they were not all powered for this outcome variable, and the study protocols were not standardized for all patients. The time to state the date of birth was chosen, since this variable requires the most conscious answer compared to the other emergence variables. This primary outcome time variable is defined as time between cessation of anesthesia (T_0_) until the patient is able to state his/her date of birth on command (given every 20 sec.) and will be measured in minutes and seconds.

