### Sample size

Sample-size estimates for both considerations (superiority and noninferiority) were calculated separately. All sample sizes were calculated using a type 1 error, α = 0.05, and power of 0.80. The primary outcome calculations were carried out based on a one-way analysis of variance (same n) with three groups. The variances and means were estimated for the primary outcome variable time to state the date of birth from our meta-analysis [4]. For the sevoflurane, propofol and desflurane groups, means were set to 8.75, 6.8 and 5.6 minutes, respectively. A standard deviation of 3 minutes was considered (these parameters correspond to an effect size (f) of 0.43). A sample size of 19 patients per group is needed to detect such an effect for our superiority hypothesis.

The sample size for the noninferiority hypothesis was calculated based on the secondary outcome variable cough overall (CO). Using the normal approximation to the binomial and assuming a proportion of the outcome in the population between 0.07 and 0.10 and noninferiority bound of 0.20 a sample size of 81 and 112, respectively, is required to claim noninferiority. The margin delta of 20 % was chosen for clinical considerations. We claim that a difference of cough occurrence up to 20 % is clinically not relevant. This is justified by the result of our meta-analysis [4], where the identified coughs had never lead to a serious impact on the patients’ outcomes.

The sample size calculation for noninferiority of treatment is based on a sample size formula published by Blackwelder [7]. Considering data from the literature, a dropout rate of 5 patients per group (for example, requirement of endotracheal intubation, protocol deviations and losses for first postoperative day- follow up) is expected. We decided therefore to include 117 patients per group, to cover the calculated sample size of 19 + 5 patients per group for the superiority hypothesis as well as 112 + 5 patients for the noninferiority hypothesis. Altogether, there will be 351 randomized patients.

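### The noninferiority comparison of intraoperative cough has no per-protocol check, because the PP set is optional and assigned only to the superiority endpoint

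*Protocol article*

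**What the plan says.** Four statements under Statistical methods fix the analysis sets.

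- The general rule: "All efficacy, safety and economical results will be presented on the Intention to Treat (ITT) data set". That set is all randomized patients.
- The status of the PP set: "In case it appears necessary, we will define a secondary Per Protocol (PP) data set prior to the database lock".
- Its only stated use: "This PP data set would be used for the secondary supportive analysis of the primary efficacy criterion".
- The section closes with "Additional analyses are not planned".

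The primary criterion is a superiority question. Under Primary outcome measures the trial asks "whether the emergence time until the stating of the date of birth after desflurane anesthesia is superior" to the time after the other two agents. Noninferiority concerns intraoperative cough, listed under Secondary outcome measures with a noninferiority design and described there as powered. Under Sample size it is the governing calculation: 112 + 5 patients per group, against 19 + 5 for superiority. On how noninferiority will be judged, Statistical methods says only "The inference for the noninferiority will be based on the upper confidence bound". No analysis set is named for it beyond the ITT rule.

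**The concern.** For superiority, analysing everyone as randomized is usually the cautious choice, since departures from assigned treatment tend to shrink a difference. For noninferiority the same shrinkage works in favour of the claim. A trial that makes both claims therefore most needs its PP check on the noninferiority endpoint. Here the check, if made at all, goes to the endpoint where ITT is already the cautious analysis.

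At stake is one of the two study purposes named under Objectives and study design. If departures made the arms more alike on cough, no planned analysis would show it. Whether a PP set exists at all also rests on a later judgement of necessity for which the article gives no criterion.

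**Working it through.** **Inputs from the protocol article**

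- Sample size: type 1 error 0.05 (sidedness not stated), power 0.80, cough rate 0.07 to 0.10, margin 0.20, stated n of 81 and 112, 5 expected dropouts per group, 117 randomized per group.
- Interventions - modifications: patients whose study treatment is modified or stopped are retained, so they count in ITT.

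**The plan's own figure first.** With equal true rates p and margin δ, n per group = 2p(1 − p)(1.645 + 0.842)²/δ², at one-sided 0.05.

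- δ = 0.20: 20.1 for p = 0.07 and 27.8 for p = 0.10, so 21 and 28.
- δ = 0.10: 80.5 and 111.3, so 81 and 112.

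The stated 81 and 112 thus match a difference of 0.10, not the stated margin of 0.20. That is a separate matter to reconcile. It is noted here only because it explains why results for 0.10 are shown beside those for 0.20.

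**Model for the ITT-only analysis (assumed, not in the document).** Among adherent patients the true excess equals the margin m, so a noninferiority claim about them would be false. A share q of patients in each arm deviates and shows no difference between arms. Then:

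- ITT difference: d = m(1 − q)
- SE = √[p(1 − p)/n + (p + d)(1 − p − d)/n]
- P(claim noninferiority) = Φ((m − d)/SE − 1.645)

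**Stated margin, m = 0.20, p = 0.10, n = 112**

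- q = 0: d = 0.200, result 0.050.
- q = 5/117 = 0.043: d = 0.1915, SE = 0.0515, (m − d)/SE = 0.166, Φ(−1.479) = 0.070.
- q = 0.10: d = 0.180, SE = 0.0510, (m − d)/SE = 0.392, Φ(−1.253) = 0.105.

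**Range over the other inputs**

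| Setting | q = 5/117 | q = 0.10 |
|---|---|---|
| m = 0.20, p = 0.10, n = 117 | 0.070 | 0.107 |
| m = 0.20, p = 0.07, n = 117 | 0.072 | 0.112 |
| m = 0.10, p = 0.10, n = 112 | 0.060 | 0.076 |
| m = 0.20, p = 0.10, n = 117, one-sided 0.025 | 0.037 | 0.060 |

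The share of 10 % is an assumption. Only 5 of 117 comes from the plan, and part of that is loss to first-postoperative-day follow-up, which cannot affect intraoperative cough. In this model an analysis restricted to adherent patients stays at the nominal level.

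**Can a PP analysis be afforded?** With 117 − 5 = 112 per group, p = 0.10 and no true difference, SE = √(2 × 0.10 × 0.90/112) = 0.0401. Per comparison:

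- margin 0.20, one-sided 0.05: Φ(0.20/0.0401 − 1.645), above 0.99;
- difference 0.10, one-sided 0.05: Φ(2.494 − 1.645) = 0.80;
- difference 0.10, one-sided 0.025: 0.70.

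**The case against.** **Left to the SAP.** Statistical methods promises a full, public SAP before unmasking, and Dissemination policy commits to the CONSORT extension for noninferiority trials. Detailed rules for PP membership can indeed wait for the SAP. The allocation cannot be treated the same way: the article already gives the PP set its single use and says that no additional analyses are planned. A SAP that applied PP to cough would depart from this text.

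**The effect is small, and PP has its own bias.** Both points stand. Exposure is one short anesthetic, modification is not expected, and at 5 per 117 the inflation is about two percentage points. Excluding patients after randomization can itself remove events. That is why PP should stand beside ITT and not replace it.

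**Two stronger readings that the document does not support.**

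- A reader might infer that the plan removes intubated patients from ITT, because Sample size lists reasons for dropout ("for example, requirement of endotracheal intubation, protocol deviations and losses for first postoperative day- follow up"). That passage only enlarges the sample. ITT is all randomized patients, modified or discontinued patients are retained, and Premature study termination says that withdrawals could cost only PQRS data. Loss of coughing patients through exclusion would be a hazard of a badly defined PP set, not of ITT.
- A reader might also infer that propofol boluses dilute the comparison and that a PP set would expose this. General interventions for all patients allows them: "If indicated additional bolus injection of propofol is permissible in patients". The same section provides for an alternative airway after a second failed LMA placement. Neither is clearly a major deviation, so a PP set would not necessarily exclude these patients.

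**Conclusion.** The point holds as a modest weakness in what the article fixes. The endpoint that sets the sample size has no PP check, while the superiority endpoint may get one. At the stated margin of 0.20, with 10 % comparator cough and one-sided 0.05, ITT alone would raise false noninferiority from 5 % to about 7 % at the plan's own 5 per 117, and to about 10.5 % if 10 % deviated.

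These figures rest on three assumptions: deviating patients show no difference between arms, deviation is equally common in each arm, and false means false for adherent patients. If deviations do not dilute the difference, ITT shows no inflation. The direction is a tendency, not a certainty. The textual finding does not depend on the model.

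**What to change.** In Statistical methods:

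1. Delete the condition that makes the PP set depend on apparent necessity. Define the set unconditionally, with membership fixed before database lock and blind to arm and outcome.
2. State that noninferiority of intraoperative cough will be analysed in both ITT and PP, and claimed only if the two agree.
3. State that patients who are intubated, converted to another airway or sent to intensive care after an airway reaction are not excluded from either set for that reason. Analyse their recorded intraoperative cough, and do not count conversion itself as cough.

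The cost is one extra analysis, a few sentences, and a slightly lower chance of claiming noninferiority. No extra patients are needed.

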### Other secondary objectives

Other secondary objectives are to determine the influence of gender on the patients’ reactions, the anesthesia safety variables including hemodynamic stability, the frequency and quantity of postoperative nausea, vomiting and pain, the discharge times, the pharmacoeconomics and the recovery on the first postoperative day (1^st^ POD).

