### Participant timeline

A participant chart is shown in Additional file 1. Eligible patients, scheduled for surgery, will be presented to the anesthesia department for the general anesthesia consent preoperatively. Additionally, a blinded sub-investigator will explain the nature and purpose of the study to these patients and seek a written informed consent for the study (time point A, before surgery). The same investigator will collect the following baseline characteristics after the patient enrollment (time point A):AgeSexWeightHeightBMISmoking status (nonsmoker, current smoker-amount of pack years, ex-smoker)Contraceptives (woman - yes/no)Pre-existing diseases and medical/surgical historyClassification according to the American Society of Anesthesiologists (ASA)Apfel ScoreBaseline (Postoperative Quality Recovery Scale) PQRS testing prior to surgery (see Additional file 2)

Shortly before surgery on the same day (time point B), an unblinded investigator will randomize the patients with sequentially numbered, opaque, sealed envelopes (SNOSE).

The same unblinded investigator will perform anesthesia (time point C, surgery) and assess the intraoperative variables in the respective patient:Depth of anesthesia (BIS)Standard safety parameters: ECG, SpO_2_ and end-tidal CO_2_, and NIBPVentilation pressure parameters: Ppeak, Pmean, and PEEPType of performed surgeryRecording of the end-expiratory applied volatile anesthetic concentration/applied amount of propofol for maintenancePharmacoeconomics: Total amount of intraoperative required catecholamines, of additionally applied propofol as rescue medication, of wasted propofol at the end of the surgery in the propofol group and of intraoperative remifentanil and piritramide consumption.Time points of anesthesia induction, LMA insertion, administration of the study treatments, anesthesia and surgery durationFrequency of intraoperative (induction/maintenance) coughs and laryngospasms

The blinded investigator will enter the operating room at the time point T_0_, which starts with cessation of anesthesia and application of maximum fresh gas flow and predefines the measurement start-time point for the time variables. The unblinded investigator will ensure that the blinded individual is precluded from recognizing which anesthetic was used, by masking the ventilator. The blinded investigator will assess the following postoperative variables during time point D:

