Assessment of airway reactionsFrequency of CE and LSEEmergence times: TSB, TLR, TOE, TRC, TSNThe modified Aldrete scores with a 10-point scale will be recorded 5 minutes after removal of LMA (see Additional file 3)

Time point E starts with admission of the patient to the PACU. The blinded investigator will assess the following variables:The modified Aldrete scores with a 10-point scale will be recorded every 15 minutes until discharge from the PACU (see Additional file 3)Time-point of readiness to be discharged from the PACU (Aldrete Score ≥9) (see Additional file 3)Assessment PQRS-T40, which is 40 minutes after the time point T_0_ (see Additional file 2).The VAS pain score will be self-evaluated and recorded by 100-mm visual analog scale (VAS) (with 0 corresponding to no pain and 100 corresponding to maximal pain) every 15 minutes after admission to the PACU. For postoperative analgesia, the patients will receive 0.05 mg kg^−1^ piritramide, in order to maintain a VAS pain score ≤30 mm

Other measurements in the PACU (blinded assessor) include the following:Nausea in the PACU will be evaluated using an 11-point verbal rating scale (VRS) (with 0 corresponding to no nausea and 10 corresponding to extreme nausea) at admission and discharge from the PACU and every 15 minutes in the PACUCount of vomiting in the PACUConsumption of piritramide in the PACU

Time point E: First post-op day: (telephone interview/ visit at ward):PQRS-D1 (see Additional file 2)

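### PQRS is tested before surgery, but none of the named tests adjusts for that score; using it as a covariate would be a free, minor gain in precision

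*Protocol article*

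**What the plan says.** The Participant timeline section of the protocol article schedules PQRS three times. At time point A, the baseline characteristics collected after enrollment include "PQRS testing prior to surgery". In the PACU the blinded investigator performs "Assessment PQRS-T40, which is 40 minutes after the time point T_0", and the first-day contact by telephone or on the ward includes "PQRS-D1 (see Additional file 2". The Discussion adds that first-day testing is meant for all patients.

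PQRS is the last item under Other outcome measures. The matching objective, "the recovery on the first postoperative day (1^st^ POD", stands under Other secondary objectives.

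The Statistical methods section has one generic sentence on tests: "Parametric data will be analyzed with ANOVA and nonparametric data with the two-tailed Fisher’s exact test if incidence <5", with chi-square for larger counts. Inference for noninferiority rests on a confidence bound. The section names no covariate and does not mention PQRS. It also states "A fully specified Statistical Analysis Plan will be made public before unmasking results" and "Additional analyses are not planned".

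**The concern.** A scale measured before treatment and again afterwards usually correlates with itself within patients. Eligible patients are 18 to 75 years old with ASA status 1 to 3, so their preoperative levels may well differ, although the article gives no PQRS distribution. If follow-up scores are compared by plain ANOVA, differences between patients that existed before anesthesia stay in the error term. The intervals for desflurane against sevoflurane and propofol are then wider than the collected data allow.

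The Abstract presents first-day recovery as something the trial will add to knowledge, and the Discussion says that few earlier trials assessed it. Sites already do the work of preoperative testing. At stake is the precision of one lower-tier comparison.

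**Working it through.** **Inputs from the article.** Type 1 error and power: "All sample sizes were calculated using a type 1 error, α = 0.05, and power of 0.80" (Sample size). There are three equal groups of 117, or 112 after the five expected dropouts per group; that allowance includes first-day losses. The article gives no standard deviation, correlation, target difference or power for PQRS.

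**The plan's own ANOVA figure.** The primary sample size uses a one-way ANOVA without covariate. With means 8.75, 6.8 and 5.6 minutes, the grand mean is 7.05 and the squared deviations are 2.89, 0.0625 and 2.1025. So f = √(5.055 / 3) / 3 = 0.433 (stated: 0.43). The noncentral F distribution gives power 0.795 at 18 per group and 0.819 at 19, so the stated 19 is reproduced. It concerns time to state the date of birth, and nothing below changes it.

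**PQRS as a continuous score.** Let ρ be the correlation between the preoperative and follow-up score (assumed, with a range). In units of the unadjusted follow-up variance:

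- Raw-score ANOVA: factor 1.
- ANCOVA on the preoperative score: factor 1 − ρ² (ignoring the one degree of freedom spent).
- Change-score ANOVA: factor 2(1 − ρ), if the variances before and after are equal.
- Change score relative to ANCOVA: 2(1 − ρ) / (1 − ρ²) = 2 / (1 + ρ), which exceeds 1 for every ρ below 1.

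For one pairwise comparison with 112 per arm and two-sided α = 0.05, the difference detectable without adjustment at 80 % power is (1.960 + 0.842) × √(2/112) = 0.374 SD. With ANCOVA it is 0.374 × √(1 − ρ²). Power at 0.374 SD is Φ(2.802 / √(1 − ρ²) − 1.960). The equivalent unadjusted sample size is 112 / (1 − ρ²).

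| Assumed ρ | ANCOVA factor | Detectable difference (SD) | Power at 0.374 SD | Equivalent n per arm | Change-score factor | Change score ÷ ANCOVA |
|---|---|---|---|---|---|---|
| 0 | 1.00 | 0.374 | 80.0 % | 112 | 2.0 | 2.00 |
| 0.1 | 0.99 | 0.373 | 80.4 % | 113 | 1.8 | 1.82 |
| 0.3 | 0.91 | 0.357 | 83.6 % | 123 | 1.4 | 1.54 |
| 0.5 | 0.75 | 0.324 | 89.9 % | 149 | 1.0 | 1.33 |
| 0.7 | 0.51 | 0.267 | 97.5 % | 220 | 0.6 | 1.18 |

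The 80 % starting point is a yardstick, because the article does not power PQRS. Two results hold without knowing ρ. ANCOVA is never less precise than raw-score ANOVA, apart from the one degree of freedom. It is more precise than change-score ANOVA for every ρ below 1. A change score is itself worse than ignoring baseline when ρ is below 0.5.

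**The case against.** The strongest reply is that no PQRS analysis is stated at all. The Statistical methods sentence only matches tests to data types. ANOVA of a change from baseline, or chi-square on returned or not returned to baseline, would use the preoperative score within the named tests. The outcome is described as recovery and the preoperative test is labeled baseline, so such a reading is natural. The scoring form is in an additional file that is not shown. This stands: a reader might infer that the plan discards the baseline score, but the article does not say so. The statement that no additional analyses are planned does not settle it either, since it does not say how the planned PQRS comparison is set up.

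A second reply is that covariates for a lower-tier outcome belong in the analysis plan, which the article promises. That is fair, and the plan may already include the adjustment. The absence of this detail is therefore no fault in itself. What remains is that the methods the article does name carry no baseline term, and a better one is available from data already collected.

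A reader might also infer that chance imbalance in preoperative PQRS would bias the comparison. It would not: randomization keeps the unadjusted comparison unbiased, and its type 1 error already allows for chance imbalance.

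Finally, the gain is hypothetical. No correlation is given, at ρ = 0.1 the benefit is practically nil, and the arithmetic treats PQRS as continuous, which the article does not establish.

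**Conclusion.** The point holds as a minor efficiency improvement. It is not a defect of validity, and it changes no figure in the article. If T40 and first-day PQRS are compared as continuous scores, ANCOVA on the preoperative score lowers the variance by 1 % to 49 % over assumed correlations of 0.1 to 0.7, and the article offers nothing to narrow that range. Its advantage over a change-score analysis rests on equal variances before and after surgery. If PQRS is reported only as recovered or not relative to baseline, the preoperative score already enters the outcome definition and these figures do not apply.

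**What to change.** In Statistical methods or the promised analysis plan, before results are unmasked:

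1. Say which PQRS value is compared: raw score, change, or return to baseline.
2. For T40 and first-day PQRS scores analyzed as continuous, specify ANCOVA with treatment and the time-point-A PQRS score as covariate.
3. Report the adjusted differences of desflurane against sevoflurane and against propofol, with confidence intervals.
4. If PQRS is analyzed only as recovered or not relative to baseline, a logistic model with treatment and baseline score is optional.

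The cost is a few lines of wording and one degree of freedom. No visit, measurement or patient is added. Adjustment introduced only after unmasking would be post hoc.
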